## 7.2 Procedures at each Visit

### 7.2.1 Overview of Study Visits

**Table 6:** Scheduled study visits of TBRU-dS-BA-PIIb

| Study Visits TBRU-dS-BA-PIIb |       |                                 |                                                          |
|------------------------------|-------|---------------------------------|----------------------------------------------------------|
| Study Period                 | Visit | Purpose                         | Time range                                               |
| Pre-treatment phase          | 1     | Screening                       | N/A                                                      |
|                              | 2     | Biopsy Harvesting (Biopsy Nr.1) | N/A                                                      |
|                              | -     | IMP Manufacturing               | From date of biopsy to grafting                          |
| Treatment phase              | 3     | Grafting                        | Day 0 (max. -1 day before grafting for some assessments) |
|                              | 4     | First graft check               | 6-10 days post grafting                                  |
|                              | 5     | Second graft check              | 21 ± 2 days post grafting                                |
|                              | 6     | Third graft check               | 28 ± 3 days post grafting                                |
| Post-treatment phase         | 7     | Follow-up                       | 60 ± 3 days post grafting                                |
|                              | 8     | Follow-up                       | 90 ± 5 days post grafting                                |
|                              | 9     | Follow-up                       | 6 months ± 10 days post grafting                         |
|                              | 10    | Follow-up                       | 1 year ± 30 days post grafting                           |
| Long-term follow-up          | 11    | Long-term follow-up             | 2 years ± 30 days post grafting                          |
|                              | 12    | Long-term follow-up             | 3 years ± 30 days post grafting                          |

#### 7.2.2 Visit 1 - Pre-treatment phase (Screening)

Screening of patients is carried out based on the following:

- Informed Consent signed by patient/parents/legally authorized representative and Investigator
- Checking of inclusion and exclusion criteria
- Screening laboratory (HIV, HBV, HCV, and Syphilis) and pregnancy test (only in female patients post menarche or >14 years old and premenopausal patients (whereas premenopausal is defined as: <2 years after last menstruation and not surgically sterile))

Additional assessments:

- Demographic data (age, gender, ethnicity\*)
- Medical history (include previous and current diseases, co-existing diseases, history of skin lesions, previous procedures/interventions regarding skin lesions, information regarding all current medications from visit 1 on)
- Physical examination
- Vital signs (heart rate, temperature, blood pressure)
- Routine laboratory (blood count and C-reactive Protein (CrP))
- Assessment/reporting of concomitant therapy

\*Ethnicity will be assessed given the well-known relationship between various ethnicity-related skin types and risk of hypertrophic and keloid scar formation.

### 7.2.3 Visit 2 - Pre-treatment phase (Biopsy)

The following assessments have to be done prior to the biopsy harvest:

- Checking inclusion and exclusion criteria (still expected that  $\geq 90$  cm^2 of wound will remain open at 4 weeks post burn despite standard of care treatment; concomitant medical conditions; check results of screening laboratory tests and pregnancy test (if indicated))
- Vital signs (heart rate, temperature, blood pressure)
- Assessment/reporting of concomitant therapy
- Assessment/reporting of adverse events

In case the patient is eligible as required, a biopsy is performed.

- Skin biopsy (Biopsy Nr.1): Standard procedure of harvesting a split-thickness skin biopsy (or full-thickness skin biopsy in special cases after written confirmation of the manufacturer) of 4 cm^2 (as precise as possible)

In the case of a performed biopsy, but unsuccessful manufacturing process, a second biopsy can be harvested if the patient and/or parents/legally authorized representative consent to it.

In exceptional cases, at the discretion of the PI and after consultation with the Coordinating Investigator, the biopsy harvesting can be performed before the screening laboratory test results are available. This is based on the following rationale:

- HIV, HCV, HBV, and Syphilis screening laboratory is not performed for the patient's safety, but due to GMP regulation.
- HIV, HCV, HBV, and Syphilis test results must be available before the biopsy can be processed at the manufacturing site.
- In acute patients, time is very critical for the treatment process. Obtaining the screening results and shipping of the biopsy to the manufacturing site both usually take at least 24 hours each. Therefore, in severe burn patients, it can be in the interest of the patient to proceed with the biopsy harvesting without waiting for the screening laboratory, as long as the screening laboratory results will be available when the biopsy arrives at the manufacturing site.

Such procedure must be clearly documented in the Investigator Site File (ISF).

### 7.2.4 Visit 3 - Treatment phase (Grafting, day 0)

The treatment phase of the study is subsequent to the successful manufacturing process of EHSG-KF and comprises the assessment of baseline parameters and the grafting of EHSG-KF or STSG alone onto the wound bed during a surgical intervention.

Following assessments can be done maximally 1 day before grafting or on the day of grafting:

- Checking inclusion and exclusion criteria
- Assessment/reporting of concomitant therapy
- Physical examination
- Routine laboratory (blood count and CrP)

Following assessments have to be done on the day of grafting (day 0):

- Vital signs (heart rate, temperature, blood pressure)
- Wound swabs and clinical evaluation for signs of infection at the study areas
- Photographic documentation of study areas (before and after wound bed preparation, and after application of the control STSG and EHSG-KF)
- Assessment/reporting of adverse events
- Determination and randomisation of study areas (experimental and control areas)

- Facultative biopsies from each wound bed (experimental area and control area) before and after wound bed preparation (e.g. necrectomy, excision) prior to grafting for histological examination of the wound ground.
  - One representative punch biopsy in both wound areas (experimental and control areas) before preparing the wound bed (Biopsies Nr. 2 and 3)
  - Another punch biopsy (experimental and control areas) will be taken after preparing the wound bed (Biopsies Nr. 4 and 5)
- Grafting in the operation theatre
- Plan postoperative visit 4 (6-10 days post grafting)

#### **7.2.5 Visit 4 - Treatment phase (First Graft Check, day 6-10)**

- Assessment/reporting of concomitant therapy
- Assessment/reporting of adverse events
- Photographic documentation of study areas
- Vital signs (heart rate, temperature, blood pressure)
- Routine laboratory (blood count and CrP)
- Dressing change
- Assessment/reporting of local infection rate, including wound swabs and clinical evaluation for signs of infection
- Assessment of the graft take (percentage of the whole grafted area)
- Plan postoperative visit 5 ( $21 \pm 2$  days post grafting)

#### **7.2.6 Visit 5 - Treatment phase (Second Graft Check, day $21 \pm 2$ )**

- Assessment/reporting of concomitant therapy
- Assessment/reporting of adverse events
- Photographic documentation of study areas
- Vital signs (heart rate, temperature, blood pressure)
- Dressing change
- Assessment/reporting of local infection rate, including wound swabs and clinical evaluation for signs of infection
- Assessment of epithelialisation of study areas
- Plan postoperative visit 6 ( $28 \pm 3$  days after grafting)

#### **7.2.7 Visit 6 - Treatment phase (Third Graft Check, day $28 \pm 3$ )**

- Assessment/reporting of concomitant therapy
- Assessment/reporting of adverse events
- Photographic documentation of study areas
- Vital signs (heart rate, temperature, blood pressure)
- Dressing change
- Assessment/reporting of local infection rate, including wound swabs and clinical evaluation for signs of infection
- Planimetric analysis of the covered (healed) surface area of the experimental area and the control area. Assessment of the ratio of covered surface area to biopsy site or donor site surface area
- Assessment of epithelialisation of study areas and wound closure
- Plan postoperative visit 7 ( $60 \pm 3$  days after grafting)

#### **7.2.8 Visit 7 - Post-treatment phase (Follow-up, day 60 ± 3)**

- Assessment/reporting of concomitant therapy
- Assessment/reporting of adverse events
- Photographic documentation of study areas
- Vital signs (heart rate, temperature, blood pressure)
- Assessment of epithelialisation of study areas and wound closure
- Plan postoperative visit 8 (90 ± 5 days after grafting)

#### **7.2.9 Visit 8 - Post-treatment phase (Follow-up, day 90 ± 5)**

- Assessment/reporting of concomitant therapy
- Assessment/reporting of adverse events
- Photographic documentation of study areas
- Vital signs (heart rate, temperature, blood pressure)
- Assessment of scar quality of EHSG-KF in comparison to STSG alone using
  - Cutometer®
  - POSAS-questionnaire
  - DSM ColorMeter®-Measurement
- Optional biopsies: one from the experimental area and one from the control area (biopsies Nr. 6 and 7), for routine histology and immuno-histochemistry
- Assessment of epithelialisation of study area and wound closure
- QOL questionnaires
  - EQ-5D and BSHS-B for patients ≥18 years
  - EQ-5DY and PedsQL for patients <18 years
- Plan postoperative visit 9 (6 months ± 10 days after grafting)

#### **7.2.10 Visit 9 - Post-treatment phase (Safety-Follow-up, 6 months ± 10 days)**

- Assessment/reporting of concomitant therapy
- Assessment/reporting of adverse events
- Photographic documentation of study areas
- Vital signs (heart rate, temperature, blood pressure)
- Assessment of epithelialisation of study area
- Assessment of scar quality using
  - Cutometer®
  - POSAS-questionnaire
  - DSM ColorMeter®-Measurement
- QOL questionnaires
  - EQ-5D and BSHS-B for patients ≥18 years
  - EQ-5DY and PedsQL for patients <18 years
- Health Costs after a Skin Transplantation
- Plan postoperative visit 10 (1 year ± 30 days after grafting)

#### **7.2.11 Visit 10 - Post-treatment phase (Safety-Follow-up, 1 year ± 30 days)**

- Assessment/reporting of concomitant therapy
- Assessment/reporting of adverse events
- Vital signs (heart rate, temperature, blood pressure)

- Photographic documentation of study areas
- Assessment of scar quality using
  - Cutometer®
  - POSAS-questionnaire
  - DSM ColorMeter®-Measurement
- Surface area measurements (cm^2) for study areas via digital image analysis (to obtain a baseline value to calculate % change with growth)
- Physical examination
- QOL questionnaires
  - EQ-5D and BSHS-B for patients ≥18 years
  - EQ-5DY and PedsQL for patients <18 years
- Health Costs after a Skin Transplantation
- Optional biopsies: one from the experimental area and one from the control area (biopsies Nr. 8 and 9), for routine histology and immuno-histochemistry
- Plan postoperative visit 11 (2 years ± 30 days after grafting)

#### **7.2.12 Visit 11 - Post-treatment phase (Safety-Follow-up, 2 years ± 30 days )**

- Assessment/reporting of concomitant therapy
- Assessment/reporting of adverse events
- Photographic documentation of study areas
- Vital signs (heart rate, temperature, blood pressure)
- Assessment of scar quality using
  - Cutometer®
  - POSAS-questionnaire
  - DSM ColorMeter®-Measurement
- QOL questionnaires
  - EQ-5D and BSHS-B for patients ≥18 years
  - EQ-5DY and PedsQL for patients <18 years
- Health Costs after a Skin Transplantation
- Plan postoperative visit 12 (3 years ± 30 days after grafting)

#### **7.2.13 Visit 12 - Post-treatment phase (Safety-Follow-up, 3 years ± 30 days)**

- Assessment/reporting of concomitant therapy
- Assessment/reporting of adverse events
- Photographic documentation of study areas
- Vital signs (heart rate, temperature, blood pressure)
- Assessment of scar quality using
  - Cutometer®
  - POSAS-questionnaire
  - DSM ColorMeter®-Measurement
- QOL questionnaires
  - EQ-5D and BSHS-B for patients ≥18 years
  - EQ-5DY and PedsQL for patients <18 years
- Surface area measurements (cm^2) for study areas via digital image analysis (to obtain post-growth value to calculate % change with growth)

## **7.3 General Description of Study Procedures**

### **7.3.1 Recruitment Procedure**

Recruitment and screening of patients will be done by the Investigators during hospitalisation for an acute injury.

The patient or the parents/legally authorized representative will be invited to sign an informed consent and then will proceed with a screening visit to confirm the inclusions/exclusion criteria. To check the exclusion criteria of underlying medical conditions patients' histories are obtained and medical records are searched. No payments to study patients are given in compensation for time and effort of patients and/or parents/legally authorized representative.

### **7.3.2 Skin Biopsy for IMP Manufacturing**

A split-thickness healthy skin biopsy measuring 4 cm^2 (as precise as possible) is harvested before the scheduled grafting date. This biopsy is used for the manufacturing of EHSG-KF. Prior to the biopsy procedure, patient eligibility for the study must be confirmed and, whenever possible, consent will be obtained from the patient and/or parents/legally authorized representative. In emergency situations, deferred consent may be acceptable (see chapter 12.8).

Ideally, the biopsy harvesting will be done during a regular scheduled dressing change, or routine excision and grafting procedure, as early as possible during the treatment course. The biopsy is taken under routine sterile conditions by the Investigator. The decision regarding the analgosedation or anaesthesia will be patient-dependent and will be performed according to routine standards at the study centre.

A split-thickness biopsy is the preferred option and should be used if any possible. In special cases, after previous written confirmation of the manufacturer, a full-thickness biopsy can be harvested.

For a split-thickness skin biopsy, the skin is tangentially excised with a thickness of 0.2 - 0.3 mm to ensure only a superficial dermal defect is created and can therefore heal spontaneously within approximately 7-10 days. The partial thickness excision may be carried out with an electronic or air dermatome, or manually using a Goulian blade, according to the preference of the surgeon. Alternatively, the partial thickness biopsy may be cut from a STSG harvested for coverage of another site, or from a CEA biopsy, as long as it is a minimum thickness of 0.2 mm. As noted above for the full-thickness biopsy, the biopsy surface area (cm^2) will be determined and recorded and this value will be used for the calculation of the primary endpoint. As noted above, an effort will be made to ensure that the surface area of the biopsy is as close to 4 cm^2 as possible. The biopsy site is then covered with an appropriate dressing, at the discretion of the surgeon.

For a full-thickness skin biopsy, the skin is sharply incised as an ellipse, for ease of closure, and is elevated in the subcutaneous plane. The site is selected according to available areas of healthy skin, and an effort will be made to conceal the resulting scar as much as possible (e.g. along the inguinal crease, or in the postauricular scalp), at the surgeon's discretion. The biopsy surface area (cm^2) will be determined and recorded and later used for the calculation of the primary endpoint (ratio of covered surface area to biopsy surface area, as per chapter 8.1). An effort will be made to ensure that the surface area of the biopsy is as close to 4 cm^2 as possible. Undermining of the skin edges may be carried out to reduce tension on the closure as needed. Closure is then carried out using either permanent or absorbable sutures, followed by a dressing as needed, at the discretion of the surgeon.

After the skin biopsy has been taken, the biopsy is immediately placed in biopsy medium, and transferred to the manufacturing facility according to the Sponsor-approved SOPs and WIs, which were developed in accordance with Quality-Management ICH Guidelines.

### 7.3.3 Laboratory Analyses

- Screening (visit 1): Screening laboratory tests and routine laboratory tests
- Grafting (visit 3): Routine laboratory tests
- First graft check (visit 4): Routine laboratory tests
- Safety examination after premature withdrawal (if applicable): Routine laboratory tests

#### Screening Laboratory Analyses:

To exclude an underlying infectious disease, the following analyses for infections will be assessed:

- HIV, HBsAg, HCV, Syphilis (4x7.5ml blood)
- Anti-HBc (10ml serum)
- In addition, a pregnancy test will be performed in female patients older than 14 years, or post menarche, or premenopausal (3ml blood).

#### Routine Laboratory Analyses:

To investigate the local infection rate in the blood, the following haematology tests are performed:

- Blood count (1.2ml blood)
- CrP (C-reactive Protein) (1.2ml blood)

### 7.3.4 Clinical Evaluation of Signs of Infection

For wound assessment clinical signs of infection are observed. This is done at visit 3 (prior to graft application), and post-operatively at visits 4, 5 and 6.

Clinical infection may be suspected when the following signs and symptoms are observed: swelling, heat, redness, pain, loss of function, purulent discharge or increased exudate, wound deterioration and/or fever.

Clinical assessment is evaluated using subjective (clinical evaluation by an experienced surgeon) and objective (microbiological wound swabs) measures. However, the clinical evaluation by an experienced surgeon is the most important element of this assessment. Microbial colonization is almost universal in the case of severe burns, and thus microbial swabs alone cannot be used to diagnose infection. Microbial swabs are carried out to supplement the clinical findings and, when infection is present, to help guide antibiotic therapy. For classification, Investigators will distinguish between contamination, colonisation and infection, as defined in Table 7.

**Table 7:** Overview Clinical Evaluation of Signs of Infection

| Visit   | Findings                                                                                                                      | Evaluation    |
|---------|-------------------------------------------------------------------------------------------------------------------------------|---------------|
| 3       | There are no microbes                                                                                                         | N/A           |
|         | There are microbes (consistent with normal skin flora) but no signs of inflammation                                           | Colonisation  |
|         | There are microbes (not consistent with normal skin flora) but no signs of inflammation                                       | Contamination |
|         | There are microbes and signs of inflammation                                                                                  | Infection     |
| 4, 5, 6 | There are no microbes                                                                                                         | N/A           |
|         | There are microbes that were already detected on the wound swabs at the previous visit and there are no signs of inflammation | Colonisation  |
|         | There are microbes that were not detected on the wound swabs at the previous visit and there are no signs of inflammation     | Contamination |
|         | There are microbes and signs of inflammation                                                                                  | Infection     |

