### 6.3 Secondary Endpoints

Safety and efficacy evaluation, as a comparison between the EHSG-KF and control sites, based on:

- Main secondary safety endpoint:
  - Clinical and microbiologic signs of infection at visits 4 (6-10 days post grafting) and 5 ( $21 \pm 2$  days post grafting)
- Main secondary efficacy endpoints: Scar quality at the study areas
  - Assessment of elasticity of the study areas using the Cutometer® at visit 10 (1 year  $\pm 30$  days post grafting)
  - Assessment of general scar quality at the study areas using the POSAS, a reliable and validated scar assessment tool, at visit 10 (1 year  $\pm 30$  days post grafting)
- Other secondary safety endpoint:
  - Assessment and reporting of all observed adverse events will be carried out for the full duration of the study from visit 2 on
- Other secondary efficacy endpoint:
  - Epithelialization at visit 6 ( $28 \pm 3$  days post grafting)

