### 8.2.7 Clinical Signs of Infection

The local infection rate is evaluated using clinical evaluation by an experienced surgeon. Supplementary wound swabs will be carried out as noted in chapter 7.3.4. Since all severe local infections lead to poor graft take, there is a direct correlation between graft take and infection rate.

The local infection rate is assessed during the first and second dressing changes (visit 4, 6-10 days post grafting and visit 5,  $21 \pm 2$  days post grafting) as secondary endpoints, and the third dressing change (visit 6,  $28 \pm 3$  days post grafting, respectively) as an exploratory endpoint.

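### Table 7 makes a positive swab necessary for the label Infection, against the protocol's own clinical definition, so the main secondary safety endpoint can miss culture-negative infections

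*Protocol*

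**What the plan says.** Section 6.3 names the main secondary safety endpoint as "Clinical and microbiologic signs of infection at visits 4 (6-10 days post grafting) and 5".

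Section 7.3.4 describes the assessment as partly subjective (the surgeon) and partly objective (swabs), and ranks the two: "However, the clinical evaluation by an experienced surgeon is the most important element of this assessment". It gives the reason: "Microbial colonization is almost universal in the case of severe burns, and thus microbial swabs alone cannot be used to diagnose infection". On the role of swabs it adds: "Microbial swabs are carried out to supplement the clinical findings and, when infection is present, to help guide antibiotic therapy".

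The same section then sets the rule that investigators apply: "For classification, Investigators will distinguish between contamination, colonisation and infection, as defined in Table 7". In Table 7, at visit 3 and again at visits 4, 5 and 6, the row "There are no microbes" leads to N/A with no condition on clinical signs. The only row that leads to Infection is "There are microbes and signs of inflammation".

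Section 8.2.7, on how the endpoint is assessed, says: "The local infection rate is evaluated using clinical evaluation by an experienced surgeon". Section 4.3.2, on withdrawal before grafting, also judges infection at the study sites clinically and without a swab condition. Section 10.3.5 reduces the endpoint to whether an infection occurred on either site at each visit. It does not say whether that means the Table 7 label or the clinical evaluation.

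**The concern.** The text ranks the surgeon's evaluation first and the swab second. The table reverses this for one kind of wound. If the swab is negative, no clinical finding, including pus, a deteriorating wound or fever, can produce the label Infection. If the analysis counts that label, culture-negative infections drop out of the main secondary safety endpoint.

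A second and lesser gap lies on the other side. When microbes and inflammation are both present, the label is Infection, and no row exists for inflammation that the surgeon attributes to something else.

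With 12 evaluable patients and up to 15 randomised, each treatment contributes only 12 to 15 areas per visit, so the description of infection by treatment is sensitive to how single areas are labelled.

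**Working it through.** The protocol gives no figure to reproduce here. The check is a reading of the rule, an enumeration of what it can return, and an illustration on stated assumptions.

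**Step 1: the rule at visits 4 to 6.**

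| Swab | Inflammation | Table 7 label |
|---|---|---|
| Negative | No | N/A |
| Negative | Yes | N/A |
| Positive, organism already seen | No | Colonisation |
| Positive, organism new | No | Contamination |
| Positive, either | Yes | Infection |

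A positive swab is necessary for Infection. A positive swab plus inflammation is sufficient.

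**Step 2: compare with the surgeon's conclusion.** Three swab states × inflammation yes/no × surgeon's judgement infected yes/no = 3 × 2 × 2 = 12 combinations. The label and the surgeon disagree in 6 of them:
- Four are judged infected but not labelled Infection. Two of these are swab-negative (N/A, with or without inflammation). The other two are swab-positive without inflammation (Colonisation or Contamination). These last two require a surgeon to diagnose infection with no inflammation, so I put no weight on them.
- Two are swab-positive and inflamed, judged not infected, but labelled Infection.

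This counts logical possibilities and says nothing about how often they occur.

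**Step 3: follow the label to the analysis.** 7.3.4 assigns the label by Table 7, 8.2.7 rests the infection rate on the surgeon, and 10.3.5 counts infection per site without choosing. Both routes are open, and they give different answers for the swab-negative, clinically infected area. Section 10.3.13 carries the same ambiguity to visit 6.

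**Step 4: illustration. All inputs are assumptions and none is in the documents.** Let p be the share of areas the surgeon judges infected, q the share of those that are swab-negative, f the share of uninfected areas with non-infective inflammation, and s = 0.9 the swab positivity of uninfected areas. Infected, swab-positive areas are taken to show inflammation. Then

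rate labelled Infection = p(1 − q) + (1 − p) × f × s.

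With q from 5% to 20% and f from 0 to 30%:
- p = 10%: lowest 0.10 × 0.80 = 0.08; highest 0.10 × 0.95 + 0.90 × 0.30 × 0.9 = 0.095 + 0.243 = 0.338.
- p = 20%: lowest 0.20 × 0.80 = 0.16; highest 0.20 × 0.95 + 0.80 × 0.30 × 0.9 = 0.19 + 0.216 = 0.406.

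The label can fall below or above the surgeon's rate. The expected number of missed areas per treatment and visit among 12 is 12 × p × q, from 12 × 0.10 × 0.05 = 0.06 to 12 × 0.20 × 0.20 = 0.48.

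**The case against.** The strongest reply is that Table 7 largely respects the text. A positive swab without inflammation is only colonisation or contamination, so swabs alone never diagnose infection. The step to Infection turns on inflammation, which is a clinical observation. The endpoint's name joins clinical and microbiologic signs, and an endpoint requiring both is a legitimate choice. N/A may mean only that the microbial distinction does not apply. Finally, 8.2.7 already supplies the clinical definition.

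Much of this stands. For swab-positive wounds, a reader might infer that the table overrides the surgeon. The documents do not support that in full, because a clinical sign still separates the categories. A reader might also infer that the surgeon's judgement alone decides. Section 7.3.4 ranks it first, which is weaker.

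It does not remove the negative-swab problem. Nothing says that N/A is confined to microbiology. The table is titled as a clinical evaluation and is where Infection is defined. A both-required endpoint would contradict 8.2.7. The SAP, not seen here, may name the counted variable, but it would not make the protocol's text and table agree.

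Three further points limit the consequence:
- Infection is an anticipated adverse event (9.7) and adverse events are collected from visit 2 to visit 12, so a culture-negative infection is not lost to the trial.
- Secondary p-values are strictly exploratory (10.2, 10.3.3), so no claim of success depends on this.
- If colonisation is nearly universal, negative swabs may be rare. The allowed antibiotic ointments (3.7) make them plausible, but that is an inference.

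**Conclusion.** The inconsistency is real and rests on the protocol's wording alone. Table 7 makes a positive swab necessary for Infection, while 7.3.4, 8.2.7 and 4.3.2 judge infection clinically, and 10.3.5 leaves open which is counted. The main secondary safety endpoint can therefore under-count culture-negative infections. The missing row for non-infective inflammation is a lesser gap, because the conflict with the text is weaker there.

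The size and net direction of the error cannot be derived from the documents. On the assumptions shown above, missed infections come to less than one area of 12 per treatment and visit, and labelling non-infective inflammation could offset or exceed them.

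Two stronger readings should be resisted. One is that the endpoint is in fact misclassified. The documents show only that it can be, and only if the Table 7 label is what gets counted. The other is that the rule favours the product, because 1.3.2 treats certain antibiotics as possible components of EHSG-KF and residues might suppress cultures on that side. The protocol gives no residue levels or duration, and the same table applies to both areas of each patient. A difference by treatment is a possibility that the documents do not demonstrate.

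**What to change.** Reconcile 7.3.4, Table 7, 8.2.7 and 10.3.5:

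- Split the no-microbes row of Table 7 into no clinical signs (N/A) and clinical infection, culture-negative (counted as infection).
- Record the surgeon's infected yes/no for each study area beside the Table 7 label. This also covers swab-positive inflammation judged non-infective.
- State in 10.3.5 that the clinical evaluation of 8.2.7 is the counted variable.
- Report the swab-based Table 7 classification alongside it as a supportive, more objective result. Dropping the microbiological component altogether would be a poor exchange in an open-label trial.
- For visits already completed, use only signs and evaluations recorded at the time, apply a rule fixed in advance, and report the original label too. Fresh reclassification with the allocation known would invite bias.

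The cost is one table and one eCRF item, with limited re-coding. The price in validity is some reliance on an unblinded clinical judgement, which the parallel swab-based result offsets. The change concerns how the endpoint is classified and leaves patient care untouched.
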